## Abstract

**Background:**

Misuse of prescription opioids remains a public health problem. Appropriate short-term use of these medications in opioid-naive patients is indicated in selected settings but can result in unintended prolonged opioid use (UPOU), defined as the continuation of opioid therapy beyond the period by which acute pain would have been expected to resolve. Clinical strategies aimed at preventing UPOU are lacking due to the absence of information about how this poorly understood clinical phenomenon actually develops.

**Objective:**

In this research project, 3 Clinical and Translational Science Awards (CTSA) programs (Mayo Clinic, University of Michigan, and Yale University) leveraged the conceptual framework for UPOU to investigate how patient characteristics, practice environment characteristics, and opioid prescriber characteristics facilitate or impede UPOU. All data management and analyses were conducted at a fourth CTSA program (University of Minnesota). This work was accomplished by pursuing 3 specific aims.

**Methods:**

In aim 1, opioid-naive adults receiving an initial opioid prescription were recruited for study participation. Opioid prescriptions were identified longitudinally, and patterns of use were categorized as short-term, episodic, or long-term use using established criteria. Using a prospective case-control design, patients progressing to UPOU were matched 1:1 with patients who did not develop UPOU, and differences in patient characteristics were assessed. In aim 2, clinicians who prescribed opioids to patients in aim 1 were identified and recruited for prospective assessments. Institutional and individual practice environments were assessed using a validated self-report survey. In aim 3, structural equation modeling was used to evaluate data collected in aims 1 and 2, and identified interactions were further evaluated in a large national administrative claims database.

**Results:**

Patient recruitment began on August 1, 2019. However, due to the COVID-19 pandemic, patient recruitment was slowed and intermittently interrupted over the ensuing 3-year period. As a result of regional variations in the impact of the COVID-19 pandemic on research activities, the majority of patient and clinician recruitment occurred at the Mayo Clinic site.

**Conclusions:**

Following complete data analyses, it is anticipated that electronic health record systems will be leveraged to help clinicians identify at risk patients and to develop direct-to-patient educational materials to raise awareness of the risk factors for developing UPOU.

**Trial Registration:**

ClinicalTrials.gov NCT04024397; https://clinicaltrials.gov/study/NCT04024397

**International Registered Report Identifier (IRRID):**

DERR1-10.2196/72032

## Introduction

### Background

Misuse of prescription opioids remains a public health problem [1]. Appropriate short-term use of these medications in opioid-naive patients is indicated in selected settings but can result in a previously underrecognized segue to unintended prolonged opioid use (UPOU), defined as the continuation of opioid therapy beyond the period by which acute pain would have been expected to resolve [2,3]. Clinical strategies aimed at preventing UPOU are lacking due to the absence of information about how this poorly understood clinical phenomenon actually develops.

Investigators at Mayo Clinic previously organized a group of thought leaders to develop a conceptual framework for understanding the broad array of factors potentially contributing to UPOU [4]. A conceptual framework is essential both to guide the study of this clinical problem and to identify potential targets for interventions aimed at mitigating the development of UPOU. The framework is comprised of 3 domains, including patient characteristics, practice environment characteristics, and opioid prescriber characteristics that interact to either facilitate or impede UPOU (Figure 1) [4].

**Figure 1 figure1:**
[figure not shown]
The conceptual framework for unintended prolonged opioid use.

Within each domain, potential factors, drawn from the relevant literature, moderate or mediate the influence of each domain. However, the necessary evidence within each of these domains is frequently lacking. This is critically important because 25% of patients in a population who received an initial opioid prescription proceeded to UPOU [3]. This work relied on a medical records linkage system unique to the geographically defined region, limiting the ability to perform larger studies across different patient populations. It also did not perform prospective assessment of several factors important to evaluate the proposed conceptual framework.

### Study Objectives

In this research project, 3 Clinical and Translational Science Awards (CTSA) programs (Mayo Clinic, University of Michigan, and Yale University) leveraged the conceptual framework for UPOU to investigate how the patient characteristics, practice environment characteristics, and opioid prescriber characteristics facilitate or impede UPOU. All data management and analyses were conducted at a fourth CTSA program (University of Minnesota). This work was accomplished by pursuing three specific aims.

#### Specific Aim 1

The first aim was to identify incident cases of UPOU and prospectively assess their characteristics in comparison to new opioid users who did not progress to UPOU. At each site, opioid-naive adults receiving opioid prescriptions were enrolled. Opioid prescriptions and self-reported opioid use were followed, and patients progressing to UPOU were identified in real time. A matched sample of patients who did not develop UPOU were recruited for assessment of framework elements, including biochemical confirmation of opioid use, pain-related measures of physical and emotional functioning, and medical and social histories.

#### Specific Aim 2

The second aim was to assess clinicians prescribing opioids to incident cases of UPOU and new opioid users who did not progress to UPOU. Clinicians treating patients recruited in aim 1 were recruited for prospective assessment of prescriber characteristics including questions about past training in pain management, and attitudes and beliefs about pain and opioid use. The practice environment was assessed including practice organization, practice size, and estimated proportion of patients receiving pain management services.

#### Specific Aim 3

The third aim was to evaluate the conceptual framework. Using the information gathered in aims 1 and 2, structural equation modeling (SEM) was used to evaluate the associations between framework elements in each domain. Identified interactions were further evaluated in a large nationally representative administrative claims database.

## Methods

### Study Settings and Participants

#### Overview

In specific aim 1, opioid-naive adults receiving an opioid prescription (n=780 at each site) were identified at each clinical site (Mayo Clinic, University Michigan, Yale University) and recruited for study participation. A research coordinator assisted in activating a mobile platform on each patient’s personal smartphone for purposes of providing informed consent and completion of study outcome measures. Opioid prescriptions were identified longitudinally by review of each patient’s electronic health record (EHR). Patients progressing to UPOU were identified in real time, and patterns of opioid use were categorized as short-term, episodic, or long-term use using the Consortium to Study Opioid Risks and Trends (CONSORT) criteria [5]. Patients meeting criteria for episodic or long-term use were considered to have progressed to UPOU. Characteristics associated with UPOU were used to assess framework elements, including biochemical confirmation of opioid use; pain-related measures of physical and emotional functioning; and medical, surgical, psychiatric, and social histories.

In specific aim 2, clinicians who prescribed opioids to patients in aim 1 were identified and recruited for prospective assessments. Institutional and individual practice environments were assessed using a self-report survey validated in a national sample of physicians [6].

In specific aim 3, SEM was used to evaluate data collected in aims 1 and 2 to identify the associations between framework elements in each domain. Identified interactions were further evaluated in a large national administrative claims database (OptumLabs Data Warehouse [OLDW]).

#### Study Settings

Each CTSA clinical site leveraged established resources and clinical infrastructure.

#### Mayo Clinic

Olmsted County residents who previously consented to have their medical records used for research purposes were identified using the Rochester Epidemiology Project (REP) medical records linkage system [7,8]. The REP provides access to all medical records for Olmsted County residents. The indications for opioid use in these patients were both surgical and nonsurgical pain. Patients recruited from this site reflected the characteristics of UPOU as it developed in a geographically defined population.

#### University of Michigan

The surgical specialty clinics at the University of Michigan were used to identify opioid-naive patients receiving an initial opioid prescription following common surgical procedures, including knee and hip arthroplasty, inguinal hernia repair, intra-abdominal procedures, and thoracic and breast procedures [9]. The indication for opioid use in these patients was acute surgical pain. Patients recruited from this site reflected the characteristics of UPOU as it developed in a surgical setting.

#### Yale University

Yale New Haven Health is a large health care delivery system that provides services to individuals residing in the greater New Haven, Connecticut area. The EHR was leveraged to identify opioid-naive adults receiving an initial opioid prescription. These individuals were contacted using the patient communication portal of the EHR to assess their interest in participating in the research project. The indication for opioid use among these patients was surgical and nonsurgical pain. Patients recruited from this site reflected the characteristics of UPOU as it developed in a large health care delivery system.

#### Study Participants

A total of 780 patients were approached for recruitment at each site (N=2340), and eligibility criteria for study participation are outlined in Textbox 1. Patients meeting these eligibility criteria were further categorized based on CONSORT criteria [5]. Criteria for the long-term CONSORT category included episodes of opioid prescribing lasting longer than 90 days and including 120 or more total days of supply or 10 or more prescriptions [5]. Criteria for the episodic CONSORT category included episodes lasting 90 days or longer, with total days of supply being fewer than 120 and the total number of prescriptions filled being fewer than 10. Criteria for the short-term CONSORT category included episodes of opioid prescribing lasting 90 days or fewer [5]. Although study participation was limited to adults who own a smartphone, recent data from January 2018 demonstrated 77% of US residents own a smartphone [10].

Eligibility criteria.
**Inclusion criteria:**
Age ≥18 yearsNo use of opioids for 6 months before the issuance of the initial opioid prescription as confirmed by review of the electronic health record and patient self-reportWillingness to participate in all aspects of the study including use of the mobile platform on their personal smartphone
**Exclusion criteria:**
Cancer-associated painConcurrent treatment for cancer (eg, chemotherapy and radiation therapy)Residence in an extended care facilityAny surgery or hospitalization within the past 6 monthsMental health disorders that could impede functioning in an ambulatory care setting (eg, schizophrenia and dementia)Non–English-speaking individualsNo smartphone; although study participation was limited to adults who own a smartphone, recent data from January 2018 demonstrated that 77% of US residents own a smartphone [10]

### Specific Aim 1

#### Overview

At each of the 3 sites, a total of 780 opioid-naive adults receiving an initial opioid prescription were approached for enrollment. Subsequently issued opioid prescriptions were monitored by reviewing the EHR, and patients progressing to UPOU were identified in real time. Time-matched samples of patients who did and did not develop UPOU were recruited for assessment of outcome measures.

#### Participant Recruitment

Participant recruitment was site specific. For example, the Mayo Clinic site leveraged the resources of the REP to identify a population-based cohort of potential patients who had previously provided informed consent for the use of their medical records for research purposes. Since 2002, Mayo Clinic and Olmsted Medical Center have used a proprietary software system to document and manage all prescriptions including prescriptions for opioids [11]. These two institutions provide a vast majority of medical care for Olmsted County residents [7,8,12,13]. The electronic prescription system was used to identify previously opioid-naive Olmsted County residents receiving an initial opioid prescription as previously described [3]. These individuals were contacted by telephone and invited to participate in the study. The Michigan site used resources associated with the University of Michigan Analgesic Outcomes Study (AOS) [9]. The AOS is a prospective, observational cohort registry of postsurgical acute and chronic pain outcomes. Previously opioid-naive patients in the AOS registry were invited to participate in study. The Yale University site used the EHR to identify previously opioid-naive patients receiving an initial opioid prescription. More specifically, the EHR was screened by study personnel for the issuance of any opioid prescription, and previously opioid-naive patients were contacted using the EHR patient portal system and invited to participate in the study.

#### Mobile Smartphone Platform

All study participants were assisted by study personnel in downloading the smartphone platform (CareEvolution). The smartphone platform complied with the security and privacy controls defined by the National Institute of Standards and Technology SP 800 53 Rev 5 as designated by the Federal Information Security Modernization Act. The platform was granted authorization to operate by the National Institutes of Health and is Health Insurance Portability and Accountability Act compliant [14]. The smartphone platform was used to obtain informed consent and to collect all outcome measures.

#### Timeline for Establishing Consortium to Study Opioid Risks and Trends Criteria for Opioid Use

The timeline of the study was governed, in part, by the temporal requirements for applying CONSORT criteria (Figure 2). The beginning date of an episode of opioid use was defined as the date that the initial prescription was issued, with no previous opioid prescriptions issued for the preceding 6-month time period. The end date of an episode was the date that the last dispensed medication supply was exhausted, based on the days of supply as documented in the prescription instructions with no opioid dispensing in the ensuing 6 months. Patients who continued to use opioids on day 90 following issuance of the initial opioid prescription were invited to participate in the study assessment. Although it was not possible to accurately apply CONSORT criteria for episodic or long-term use on day 90, the study assessment was performed at this time point to ensure patients were captured at the earliest stages of episodic or long-term use. The status of opioid use in these patients was monitored every month by reviewing the EHR. This approach to follow-up limits the time interval between establishment of CONSORT criteria for episodic or long-term use and the final study assessment.

**Figure 2 figure2:**
[figure not shown]
Flow diagram for establishing Consortium to Study Opioid Risks and Trends (CONSORT) criteria for opioid use.

A randomly selected group of patients meeting criteria for short-term use at day 90 were invited to participate in the study assessment. This group of patients was selected to be time-matched 1:1 to patients continuing to use opioids at day 90 (initial issue date ±2 weeks) Although it was not possible to accurately apply CONSORT criteria for short-term use until month 6 following issuance of the last prescription, the study assessment was performed at this time point to ensure that patients were captured in the earliest stages of short-term use. Because it was anticipated that the majority of the cohort would meet criteria for short-term use, it was not feasible to invite all patients to participate in the study assessment.

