#### Study Assessments

Assessments were performed at 2 time points: 3 months following dispensing of the initial opioid prescription and 9 months following dispensing of the initial opioid prescription.

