#### Verification of Opioid Status and Dose

Opioid use and dose were verified by review of pharmacy and medical records. Opioid doses were converted to daily morphine equivalents using a conversion calculator as previously reported [15-17]. The opioid status was biochemically verified with a urine toxicology screen.

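### Controls need only have been issued a prescription, although Aim 1 compares cases with new opioid users; no stated rule requires that a control filled or took the drug

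*Protocol article*

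**What the plan says.** All from the protocol article.

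- **Comparator.** Study Objectives, Specific Aim 1, sets out to identify incident cases and "prospectively assess their characteristics in comparison to new opioid users who did not progress to UPOU".
- **Entry.** The Methods Overview states that "opioid-naive adults receiving an opioid prescription (n=780 at each site) were identified at each clinical site". The eligibility textbox asks for adult age, no opioid use in the preceding 6 months and willingness to take part. Neither its inclusion nor its exclusion list mentions a fill or a dose.
- **Episode.** In the CONSORT timeline section, "The beginning date of an episode of opioid use was defined as the date that the initial prescription was issued", whereas "The end date of an episode was the date that the last dispensed medication supply was exhausted".
- **Short-term class.** Under Study Participants, "Criteria for the short-term CONSORT category included episodes of opioid prescribing lasting 90 days or fewer". There is no lower bound and no dispensing condition.
- **Selection.** Cases are patients still using opioids on day 90. For controls, "A randomly selected group of patients meeting criteria for short-term use at day 90 were invited to participate in the study assessment", matched 1:1 on issue date within 2 weeks.
- **Status.** Limitations says that case and control status was based on the number of prescriptions issued, and that this could differ from the number dispensed.
- **Dispensing and actual use.** The first study assessment falls "3 months following dispensing of the initial opioid prescription". Under Verification of Opioid Status and Dose, "Opioid use and dose were verified by review of pharmacy and medical records", with a urine screen as well. Specific Aim 1 adds that self-reported use was followed.

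**The concern.** On the issue-based rules, a person who was handed a prescription and never filled or took it qualifies as a short-term user and can be drawn as a control. That person was never a new opioid user. The day-90 rule for cases keeps such people almost entirely out of the case group.

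Aim 1 asks what separates people who progress from people who start and stop. If some controls never started, the comparison also picks up what separates people who take an opioid from people who do not. Pain intensity, pain catastrophizing, chronic pain history and misuse risk are all measured, and each could plausibly relate to taking the drug at all. For such a predictor, the odds ratio would answer two questions at once.

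**Working it through.** **1. Set the rules side by side for someone with nothing dispensed**

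| Rule | Clock or basis | Result for a never-filler |
|---|---|---|
| Cohort entry | prescription received | enters |
| Episode start | issue date | defined |
| Episode end | last dispensed supply exhausted | undefined |
| Short-term class | prescribing episode of 90 days or fewer | qualifies if prescribing is what counts; cannot be placed if the episode end is needed |
| Matching | issue date | defined |
| Assessments at 3 and 9 months | dispensing date | undefined |
| Case or control status (Limitations) | prescriptions issued | control |

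The rules disagree on whether such a person belongs in the study, and none settles it. Pharmacy review, the urine screen and self-report are described as data collected, not as conditions for being a control. A negative urine screen at month 3 cannot tell someone who stopped from someone who never started.

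**2. Reproduce the plan's own figure**

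Inputs (Specific Aim 1, Sample Size Estimates): 600 pairs, two-sided 0.05, power 0.8, prevalence 0.5 in controls, correlation 0. The expected discordant share is 0.5, so there are 300 discordant pairs. At an odds ratio of 1.385, the probability that a discordant pair has the case exposed is P = 1.385/2.385 = 0.5807. Then

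z = [(P − 0.5)√300 − 1.96 × 0.5] / √(P(1 − P)) = (1.398 − 0.98)/0.493 = 0.85, which gives power 0.80.

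This agrees with the stated 1.38. The other two stated values, 1.48 and 1.55, also reproduce (1.477 and 1.552). The sample-size arithmetic is sound; the point concerns only who counts as a control.

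**3. Effect on a predictor with no true association**

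Let f be the never-user share of controls and p the predictor's prevalence among never-users. **Neither is in the documents; both are assumptions.** Prevalence is 0.5 in cases and in true short-term users.

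Control prevalence c = 0.5(1 − f) + p·f. Apparent odds ratio = (1 − c)/c, because the case odds are 1.

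| f | p | c | Apparent OR |
|---|---|---|---|
| any | 0.5 | 0.50 | 1.00 |
| 5% | 0.3 | 0.490 | 1.04 |
| 5% | 0.2 | 0.485 | 1.06 |
| 10% | 0.3 | 0.48 | 1.08 |
| 10% | 0.2 | 0.47 | 1.13 |
| 20% | 0.3 | 0.46 | 1.17 |
| 20% | 0.2 | 0.44 | 1.27 |

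Rejection probability comes from the log odds ratio of discordant pairs. For f = 10%, p = 0.3 and 600 pairs, the discordant counts are 600 × 0.5 × 0.52 = 156 and 600 × 0.5 × 0.48 = 144. Then ln(156/144) = 0.080, its standard error is √(1/156 + 1/144) = 0.1156, and z = 0.69. The two-sided rejection rate is 10.7% against a nominal 5%. Likewise it is 28% for f = 20%, p = 0.3; 55% for f = 20%, p = 0.2; and about 6% for f = 5%, p = 0.3. With about 513 pairs (the case count in Table 1), the first three become 10%, 25% and 48%.

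**4. Direction**

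Take a true odds ratio of 1.38. With p = 0.3 and f = 10%, it becomes 1.38/(0.48/0.52) = 1.50; at f = 20%, 1.38/(0.46/0.54) = 1.62. With p = 0.7, it becomes 1.38/(0.52/0.48) = 1.27 and 1.38/(0.54/0.46) = 1.18. The bias can therefore inflate or shrink an association.

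**5. Upper limit**

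An apparent 1.38 from a null predictor needs c = 1/2.38 = 0.420. At f = 15% the lowest possible c is 0.5 × 0.85 = 0.425, so it cannot occur at or below that share. At f = 20% it needs p = (0.420 − 0.400)/0.20, about 0.10.

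**The case against.** Several objections have force.

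- **Dispensing may have been presupposed.** The episode end and the assessment dates both need a dispensing event, and pharmacy records and self-report were reviewed. The flow diagram and full protocol are not shown and may contain a fill check. A reader might infer from the issue-based wording that never-users were in fact enrolled as controls. The documents do not show that. They show only that the stated rules allow it and contradict one another.
- **The limitation is partly disclosed.** The article admits that issued and dispensed prescriptions may differ. It treats this as a general discrepancy, without noting that complete non-use would fall almost wholly on controls, and it offers no remedy.
- **Not every contrast is affected.** A reader might infer that all comparisons are distorted, or always inflated. Neither follows: with equal prevalence in never-users and users the odds ratio is unchanged at any share, and otherwise the bias can run either way.
- **The source population is defensible.** The Conclusions foresee alerts for patients given a first prescription. For that use, never-fillers belong in the comparison. This stands, but it is not the comparator that Aim 1 names.
- **Cases are not guaranteed users either.** Issue-based status applies to both groups, so any check must cover both.

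**Conclusion.** The point holds as a mismatch between the stated comparator and the stated selection rules. Under those rules never-users could enter, almost entirely as controls, and would bias odds ratios for predictors related to filling or taking the drug.

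The size is conditional. Over the assumed range in the table above, a null predictor shows an odds ratio of about 1.04 to 1.27, below the plan's detectable 1.38. The inflation of false positives is slight at a 5% share and substantial at 20%. Nothing in the documents says where in that range the study lies, or whether the share is zero. The reading that Aim 1's results are invalid throughout is not supported.

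**What to change.** 1. Reconcile the issue-based text (entry, episode start, short-term class, matching, Limitations) with the dispensing-based text (episode end, assessment timing), and state whether a fill or any use was required of controls.
2. Using the pharmacy records and self-reported use that the article describes, apply one check to cases and controls alike: confirmed dispensing or self-reported use. Report how many in each group fail. A dispensing record does not prove intake, so this check catches never-fillers more surely than people who filled and took nothing.
3. For the comparison with new opioid users, rerun the Aim 1 conditional logistic models on pairs in which both members pass. Keep the analysis of everyone issued a prescription, labelled as applying to that population.
4. Do not replace removed controls with unselected short-term users. They were not invited to the day-90 assessment, and data collection has ended.

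The cost is a record review and some lost pairs. Losing 10% of 600 pairs leaves 540, and the detectable odds ratio rises from about 1.385 to 1.41; losing 20% takes it to 1.44. Starting from 513 pairs, a 10% loss moves it from about 1.42 to 1.45.
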